#### Interviews

A member of the research team will be in charge of conducting individual semistructured interviews. For security reasons, the interviews will be carried out at the locations where participants were recruited. Each interview is expected to last approximately 1 hour. The questions that will be posed to both samples are as follows:

What does “living with CP” mean to you?How do you manage CP in your daily life?Have your self-management strategies changed over time? If yes, how?What role does your partner play with regard to your CP?Does CP affect your relationship? If yes, how?Does your partner use your health condition against you? If yes, can you provide examples?Does your relationship affect your CP? If yes, how?What is your experience with the health system?What is your relationship with medication?

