### Goals of This Study

This research project has 2 general objectives and 6 specific aims.

First, we seek to understand the meaning and implications of living with CP for women experiencing IPV compared to those with CP alone. From this point forward, the term “women with CP alone” will refer to women who have never experienced any form of psychological, physical, or sexual violence at any stage of their lives, whether perpetrated by an intimate partner or another known or unknown individual. We include other forms of violence beyond IPV against women because they may also influence CP management and health outcomes [31].

More specifically, by comparing women with CP and exposure to IPV to women with CP alone, we aim to (1) examine how CP affects their daily lives, (2) identify the impact that CP may have on their intimate relationship and vice versa, (3) understand how they self-manage CP, and (4) describe their experiences with health systems.

Second, we aim to determine whether women with CP alone, women with CP who are currently experiencing IPV, and women with CP who have a past history of IPV present distinct profiles based on risk and protective factors for disabling CP and health outcomes. If differences exist, we will also (5) identify the factors that best explain these profiles and (6) detect more specific subprofiles within each group.

Ultimately, the findings will be used to develop assessment and intervention guidelines for health and social service professionals.

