### Phase 1: Qualitative Study (General Aim 1, Specific Objectives 1 to 4)

#### Overview

We will use a qualitative approach with a descriptive and exploratory design, conducting individual semistructured interviews. Focus groups are not considered due to the necessity of maintaining the anonymity of those experiencing IPV against women. The results of this phase will allow us to incorporate any additional relevant factors or health outcomes into the study’s second phase.

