## Discussion

### Summary

This project has 2 main aims. The first is to acquire knowledge on the meaning and implications of living with CP for women experiencing IPV compared to those with CP alone. In this regard, we hypothesize that (1) women who experience any form of IPV (psychological, physical, or sexual) will report a greater daily impact of CP on their functionality than those with CP alone; (2) compared to the latter, the former will report a stronger bidirectional relationship between CP and intimate relationship dynamics as well as worse health outcomes (ie, episodes of violence will increase CP symptomatology and vice versa), with such a negative cycle being more prevalent; and (3) CP management and experiences with the health system will be better among women with CP alone. Hypotheses 1 and 3 are based on the fact that some authors have highlighted that the impact of IPV against women on the health of those affected adds to CP [31]. This could impair their ability to self-manage CP, leading to increased medication use and more frequent visits to health centers [165]. We believe that this result will be independent of the type of violence experienced because studies have shown that psychological violence alone can negatively impact CP severity and disability [166,167].

Regarding our second hypothesis, we expect that aggressors will present more hostility and criticism toward their partners’ health conditions as a way to undermine them, increase dependence, and control them, considering violence as an instrumental component [165]. We also expect that periods of violence will be linked to an increase in CP symptomatology. However, in women with CP alone, their partners will likely promote autonomy by encouraging and reinforcing healthy behaviors or promote dependence by maintaining disabling pain behaviors through solicitousness. In this group of women, even if hostile responses can also be present sometimes, their impact on CP will be less significant because they need to take place in a context of low marital satisfaction [95,96], and we assume that levels of marital satisfaction will be higher among women with CP alone. In addition, we expect that periods with an increase in CP symptomology will be more related to external stressors than to the relationship itself.

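### The listed interview questions do not systematically elicit causes of pain change other than the relationship, and the only specific partner conduct they prompt is harmful

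*Protocol article*

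**What the plan says.** Phase 1 is a qualitative study "with a descriptive and exploratory design, conducting individual semistructured interviews". The Interviews subsection introduces its list with "The questions that will be posed to both samples are as follows" and then gives nine question sets, worded identically for women experiencing intimate partner violence (IPV) and women with CP alone.

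The partner and relationship questions include an open one, "What role does your partner play with regard to your CP"; a specific one, "Does your partner use your health condition against you? If yes, can you provide examples"; and, directly after that, "Does your relationship affect your CP? If yes, how".

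In Goals of This Study, specific aim 2 is to "identify the impact that CP may have on their intimate relationship and vice versa".

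The Discussion (Summary) sets out expectations that differ by group. For women experiencing IPV, partners are expected to be hostile and critical about the health condition, and periods of violence to go with more pain. For women with CP alone, "their partners will likely promote autonomy by encouraging and reinforcing healthy behaviors" or will foster dependence through solicitousness, and "periods with an increase in CP symptomology will be more related to external stressors than to the relationship itself".

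**The concern.** The last expectation is comparative: one source of pain increases should matter more than another. To examine it, both sources need to be asked about in a similar way. The list asks directly about the relationship and leaves every other source for the woman to raise herself. If few external stressors appear in the transcripts, the analysts could not tell whether they matter little or were simply not asked about.

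Partner conduct has a similar, milder imbalance. The conduct expected in the IPV group has a direct prompt with a request for examples. The supportive or solicitous conduct expected in the comparison group has no matching prompt and depends on the general question about the partner's role.

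Phase 1 is also meant to identify further factors to carry into phase 2 (Phase 1, Overview). A factor that is not elicited in the interviews is less likely to be carried forward.

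**Working it through.** No formula applies: the point depends on no sample size, error rate or effect size. The check sets the listed questions against the aims, the stated expectations and the other instruments.

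**Step 1. The nine question sets, in order (Interviews).**

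| No. | Topic | Names an influence on pain? | Names a specific partner conduct? |
|---|---|---|---|
| 1 | Meaning of living with CP | No | No |
| 2 | Daily management | No | No |
| 3 | Change in management over time | No | No |
| 4 | Partner's role | No (open) | No (open) |
| 5 | Effect of CP on the relationship | No | No |
| 6 | Partner using the condition against her, with examples | No | Yes, harmful |
| 7 | Effect of the relationship on CP | Yes, the relationship (direction left open) | No |
| 8 | Health system | No | No |
| 9 | Medication | No | No |

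**Step 2. Counts.**
- Partner or relationship: 4 of 9 (nos. 4 to 7).
- Asks what influences the pain: 1 of 9, and it names only the relationship.
- Asks about stressors outside the relationship, or generally what makes pain better or worse: 0 of 9.
- Names a specific partner conduct: 1 of 9, harmful. Names supportive or solicitous conduct: 0 of 9. Asks openly about the partner: 1 of 9.

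**Step 3. Order.** Three open questions precede any partner question, and the neutral partner-role question comes two places before the adversarial one. The adversarial question stands immediately before the only question on what influences the pain.

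**Step 4. Set against the Discussion.**
- Relationship and pain, both directions: asked directly (nos. 5 and 7).
- Partner hostility about the condition: asked directly, with examples (no. 6).
- Partner support or solicitousness: can surface under no. 4, with no request for examples.
- External stressors as the larger source of pain increases in women with CP alone: no listed question.

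**Step 5. Do other instruments fill the gap?**
- The adapted Life Events Checklist in phase 1 is ticked in Table 1 for control purposes only. It covers potentially traumatic events such as natural disasters, not everyday stressors tied to pain increases.
- Relationship satisfaction is collected in phase 1, but it does not bear on causes of pain change.
- In phase 2, the informal social support inventory (ISSADI-PAIN) measures partner support for autonomy and dependence. It covers partner conduct there, but not what sets off pain increases. Table 2 lists no instrument on everyday stressors or triggers.

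**The case against.** The strongest case for the list as it stands has five parts.

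- **It follows the stated aims.** The four phase 1 aims are daily life, the two-way link between CP and the relationship, self-management, and health systems. External stressors are not among them, nor in the numbered statement of hypothesis 2; they appear in one supplementary sentence of the Discussion. This stands, and four of nine questions on the partner or relationship is not in itself evidence of bias. The sentence is nevertheless a stated expectation about phase 1, and nothing listed addresses it directly.
- **The format is open.** The interviews are semistructured and analysed inductively, and three open questions come first. Other causes can therefore be volunteered or probed. This stands, so a reader who infers that the contrast cannot be examined at all goes further than the protocol supports. What is missing is systematic elicitation.
- **Partner conduct is not prompted only in its harmful form.** The role question is neutral and comes earlier, and the question on whether the relationship affects CP leaves the direction open. This stands. The accurate statement is that the only *specific* conduct named is harmful.
- **Both groups get the same wording, and the adversarial question lets women with CP alone disconfirm the expectation.** This also stands. A reader might infer that accounts are in fact steered toward hypothesis 2, or that external stressors will be under-reported, but neither is shown. Identical wording does not balance the prompts, however, since only the conduct expected in the IPV group has a specific one.
- **The article condenses a fuller interview guide, whose development is a separate task in Table 3.** Unlisted probes may exist, and their absence from an article is not a fault. The point here rests on the questions the article does list, set beside an expectation it does state.

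**Conclusion.** The point holds in a limited form. The listed questions do not systematically elicit causes of pain change other than the relationship, and the one specific partner behaviour they prompt for is harmful. As listed, the expected contrast between external stressors and the relationship would rest on spontaneous remarks or on probes left to the interviewer. That brings a risk of favouring relationship explanations. Its size is unknown and cannot be derived from the protocol.

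This rests on two assumptions: that the list shows the questions to be asked, as the article presents it, and that no standard probe on pain triggers or partner support sits in the unpublished guide. If such probes exist, the remedy is only to report them. The aim 2 questions are sound and should stay. The change is worth making because it is cheap and serves an expectation the authors themselves state.

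**What to change.** For both groups, and before the other partner questions:

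1. Add one open question, ahead of the partner-role question, on when the pain gets better or worse and what the woman thinks brings this about. Causes she names unprompted are then recorded before the relationship is suggested.
2. Extend the existing partner-role question with a neutral request for examples of how her partner responds when she is in pain. It already precedes the question about the condition being used against her, so no reordering is needed.

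Keep all existing relationship questions after these. If the interviews are already done, report the external-stressor expectation as not directly assessed, and describe any material on it as volunteered or probed ad hoc.

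The cost is a few minutes of interview time (as an assumption, 5 to 10 of about 60), an updated guide and possibly an ethics notification. No extra participants or staff are needed.

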#### Instruments

The variables and instruments that will be used, organized by purpose, are summarized in Table 1 and described in the subsections that follow.

**Table 1 table1:** Variables and instruments used in study 1, organized by purpose.

Variable	Questionnaire	Control purposes^a^	Data analysis
Chronic pain	Ad hoc question	✓	
Sociodemographic characteristics	Ad hoc questionnaire	✓	✓
IPV^b^ against women	European Union Agency for Fundamental Rights study on violence against women survey inventory	✓	✓
Possible traumatic events experienced	Adapted version of Life Events Checklist for DSM-5	✓	
Disabling chronic pain	GCPS-R^c^		✓
Severity of PTSD^d^ symptoms	EGS-R^e^		✓

^a^We include compliance with the inclusion and exclusion criteria.

^b^IPV: intimate partner violence.

^c^GCPS-R: Graded Chronic Pain Scale Revised.

^d^PTSD: posttraumatic stress disorder.

eEGS-R: Escala de Gravedad de Síntomas Revisada (Posttraumatic Stress Disorder Symptom Severity Scale-Revised [according to Diagnostic and Statistical Manual of Mental Disorders, Fifth Edition criteria]).

#### Screening for Compliance With Inclusion and Exclusion Criteria

### CP and Type

To distinguish participants with acute pain from those with CP, they will first be asked how long they have been experiencing pain. Participants will also select the type of CP they experience, such as fibromyalgia, from a provided list.

### Sociodemographic Characteristics

Participants will have to indicate their age, sex at birth, gender identification, racial and ethnic identity, sexual orientation, and relationship status (whether currently in a relationship and for how long).

### IPV Against Women: European Union Agency for Fundamental Rights Study on Violence Against Women Survey Inventory

Participants will complete an inventory [127] consisting of 32 items that assess various forms of violence exerted by a partner: 11 items on physical violence, 4 on sexual violence, and 17 on emotional and psychological violence. Participants will respond with the frequency of each type of violence (0=*never*, 1=*once*, and 2=*more than once*) and specify whether the violence was inflicted by a past or current partner, including the duration of the violent relationship. A woman will be classified as experiencing current IPV or having experienced past IPV if she reports experiencing any item more than once from the same partner.

### Possible Traumatic Events Experienced: Adapted Version of Life Events Checklist for DSM-5

The original version of this checklist [128] contains 17 items referring to different stressful events. Participants will have to mark whether they have experienced, witnessed, or learned about each event; whether it was part of their job; or whether it does not apply to them. The adapted version will rephrase the items on physical and sexual assault (items 6 to 9) into a single item: exposure to “psychological, physical, and/or sexual violence or abuse at any stage of your life by a known or unknown person other than an intimate partner.”

The purpose of using this instrument is helping to control for any external traumatic events (eg, natural disasters) that may influence pain experiences different from experiencing IPV.

#### Configuration for Diverse Groups and for Data Analysis Purposes

##### Additional Sociodemographic Characteristics

Both groups of participants will need to complete a questionnaire detailing their nationality, years of education, profession, annual household and personal incomes, relationship satisfaction, and the number of children. This information will help in differentiating the groups and understanding various factors that may impact pain experiences. Regarding pain characteristics, participants will report on pain location, severity, diagnosis, and the time since they were diagnosed with CP.

##### IPV Against Women: European Union Agency for Fundamental Rights Study on Violence Against Women Survey Inventory

This inventory [127] will be used to assess the severity of violence experienced by participants, based on the total score obtained, with a maximum possible score of 64 points. The severity of the violence will be classified into 3 categories—low, moderate, and high—determined by calculating percentiles. This inventory is available in multiple European languages, including Spanish.

##### Disabling CP: Graded CP Scale Revised

For assessing disabling CP, the Graded Chronic Pain Scale Revised [129] will be used. This scale consists of 5 items, each rated on a scale ranging from 0 to 10, and provides a simple and valid method for classifying CP as mild, bothersome, or high impact. Those who, on items 1 and 2, report that in the past 3 months, their pain has limited their life activities or work on most days or every day will be classified as grade 3 (high-impact CP). Those who score ≥12 on items 3 to 5 will be classified as grade 2 (bothersome CP); and those who score <12, with no high-impact pain, will be categorized as grade 1 (mild CP). The Graded Chronic Pain Scale Revised has demonstrated good concurrent validity.

##### Severity of PTSD Symptoms: PTSD Symptom Severity Scale-Revised

This instrument [130] consists of 21 items related to the *Diagnostic and Statistical Manual of Mental Disorders, Fifth Edition* diagnostic criteria: 5 to re-experiencing symptoms, 3 to behavioral and cognitive avoidance symptoms, 7 to cognitive disturbances and negative mood, and 6 to symptoms of increased psychophysiological arousal and reactivity. The responses are rated on a 3 points Likert- type scale ranging from 0 to 3 points according to symptom frequency and intensity. When a person scores at least 2 points in an item, the symptom to which the item refers to is considered present. The overall scale ranges from 0 to 63 points. The instrument has shown high internal consistency, good discriminant and concurrent validity and diagnostic efficacy in a large sample of Spanish women who have mostly experience IPV.

#### Data Analysis

The verbatim interview transcripts will undergo inductive reflexive thematic analysis, a foundational and flexible qualitative method that allows researchers to identify, analyze, and report themes or patterns in data [131,132]. In this study, the focus will be on understanding participants’ experiences, meanings, and realities.

Two researchers trained in reflexive thematic analysis will collaborate using the process established by Braun and Clarke [131,132]. The process begins with data familiarization, where the researchers review the material and take initial notes. Next, they will systematically code the data, group similar codes, and produce initial themes based on the collated data. These themes will then be developed and revised through an iterative process. The final stage involves refining, defining, and naming the themes before writing the report. Inductive coding will be carried out using NVivo 10 software (Lumivero).

To ensure the quality of the analysis, several procedures will be implemented throughout the research. This will include ensuring that the research question aligns with the methodological decisions (ie, methodological coherence) and selecting participants who can provide the most relevant and insightful information. Data analysis will be an iterative process, allowing ideas to evolve and be confirmed with the data. In addition, the research team will work closely together to develop interpretations and concepts that best capture the phenomenon under investigation.

#### Phase 2: Quantitative Study (General Aim 2, Specific Objectives 5 and 6)

Phase 2 of the research will focus on a cross-sectional quantitative study aimed at examining the differences between 3 groups of women.

#### Participants

The reference population will include heterosexual women aged ≥18 years living in the province of Alicante. To detect possible differences in profiles, the study will be carried out in 3 groups of women: those who have CP and have never experienced IPV or any other type of violence (group 1), those who have CP and are currently experiencing IPV (group 2), or those who have CP and have a past history of IPV (group 3). It is important to note that the effects of violence may continue to impact individuals long after the relationship ends, and this study aims to identify risk and protective factors, as well as health outcomes, to support detection and intervention efforts.

#### Sample Size Calculation

To calculate the sample size, the prevalence of the pain-avoidance activity pattern was used, which is typically present in cases of highly disabling CP [102]. Specifically, we considered several factors: first, the expected prevalence ratio assumed to be 2.0 between individuals with CP who are exposed to IPV against women and those who are not. Second, we estimated the prevalence of the pain-avoidance activity pattern within the study population, assuming it to be approximately 20%. While a previous study found that 40.4% of patients with fibromyalgia exhibited this pattern [133], we decided to use a more conservative estimate, given that the prevalence of this behavior is likely lower among the broader population of patients with CP. Finally, we accounted for the expected prevalence of IPV exposure among women with CP, estimated at 30% based on findings from earlier research [23].

We have defined the risk level α as 5% and the study power as 90%. The program used for size calculation was a macro, !NSize, for SPSS Statistics [134]. On the basis of these parameters, the required sample size consists of 359 women with CP: 193 (53.8%) with CP alone, 83 (23.1%) with CP and a current history of IPV, and 83 (23.1%) with CP and a past history of IPV.

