## Introduction

### Background

Chronic pain (CP) is defined as pain that persists beyond the normal tissue healing period, typically lasting approximately 3 months. It is a major health concern affecting approximately 30% of people worldwide [1]. CP is more prevalent and burdensome among populations experiencing vulnerability, including women, older adults, children, individuals from racial or ethnic minority groups, and those from lower socioeconomic backgrounds [2,3]. In Europe, the economic burden of CP could reach up to €300 billion annually (US $343 billion) [4].

There is broad consensus that understanding and treating CP requires a biopsychosocial approach. Beyond biological and physiological factors, psychological, social, and life experiences play a crucial role in the development, exacerbation, and persistence of pain [5-7]. Notably, CP is a well-documented consequence of another public health problem, intimate partner violence (IPV) against women, as demonstrated by controlled studies in both population-based and clinical samples [8-11].

IPV against women is a gender-based issue [12-14] that encompasses physical, psychological, or sexual violence perpetrated by some men against their female partners [15]. Today, IPV against women remains a widespread epidemic, affecting at least 30% of women worldwide [16]. It has severe health and social consequences [17] and imposes an economic cost of €174 billion (US $199 billion) per year on the European Union [18].

Compared to women who have not experienced violence, those exposed to IPV against women report a higher prevalence of fibromyalgia, abdominal pain, genitourinary tract pain, pelvic and genital pain, headaches (including migraines), and back and neck pain [19-22]. A study conducted with 108 male and female patients with CP attending a rehabilitation center found that 56% had a current or past history of IPV, with more than 80% being women. Nearly 30% had experienced IPV within the previous year [23].

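### The 30% IPV exposure behind the 193:83 split is the cited study's past-year rate, not its current-or-past rate of 56%; the 90% power holds only if 20% is the CP-alone rate

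*Protocol article*

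**What the plan says.** The Sample Size Calculation section of phase 2 gives three planning inputs:

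- a ratio: "the expected prevalence ratio assumed to be 2.0 between individuals with CP who are exposed to IPV against women and those who are not";
- an outcome prevalence: "we estimated the prevalence of the pain-avoidance activity pattern within the study population, assuming it to be approximately 20" percent;
- an exposure prevalence: "the expected prevalence of IPV exposure among women with CP, estimated at 30% based on findings from earlier research [23"].

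Error rate and power follow: "We have defined the risk level α as 5% and the study power as 90" percent. The resulting targets are "193 (53.8%) with CP alone, 83 (23.1%) with CP and a current history of IPV", plus 83 with past IPV, 359 in all.

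The Background section reports the study cited as [23]. It covered 108 male and female patients at a rehabilitation center, of whom "56% had a current or past history of IPV". It adds: "Nearly 30% had experienced IPV within the previous year".

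The phase 2 Participants section defines the comparator as "those who have CP and have never experienced IPV or any other type of violence (group 1"). It gives women with past IPV a group of their own, group 3.

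**The concern.** The two accounts of the cited study do not agree. As the Background section reports it, 30% is a past-year figure. In this design exposure means current or past IPV, and both groups are sized as exposed. The figure from that study that matches this definition is 56%.

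The input matters in two ways. It sets the ratio of CP-alone to exposed women. And if the 20% is a whole-population rate, as the section words it, the exposure share also determines what pain-avoidance rate is implied for women with CP alone. That in turn sets the difference to be detected and the power.

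**Working it through.** **Inputs.** Alpha 5% (sidedness is not stated; two-sided reproduces the plan), power 90%, prevalence ratio 2.0, outcome prevalence 20%, exposure 30%, targets 193/83/83: all from the Sample Size Calculation section. Exposure 56% (current or past) and nearly 30% (past year): Background section.

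**1. Reproducing the plan.** Take p0 = 0.20 (unexposed), p1 = 0.40 (exposed) and k = 0.70/0.30 = 2.333 unexposed per exposed. The pooled rate is (0.40 + 2.333 × 0.20)/3.333 = 0.26.

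- Uncorrected: n1 = [1.960 × √(0.26 × 0.74 × (1 + 1/k)) + 1.282 × √(0.40 × 0.60 + 0.20 × 0.80/k)]² / 0.20² = (1.0275 + 0.7119)²/0.04 = 75.6.
- Continuity-corrected: n1 = (75.6/4) × [1 + √(1 + 2(1 + 1/k)/(75.6 × 0.20))]² = 82.6.
- Unexposed: 82.6 × 2.333 = 192.8.

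This gives 83 and 193. Using the 83 a second time for the other IPV group gives 193 + 83 + 83 = 359. So the published figures come from 20% as the *unexposed* rate and from 30% as the allocation: 193/276 = 69.9%. Reading 20% as the overall rate does not reproduce them; the same formula then needs 118 + 276.

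**2. What the 30% stands for.** Its complement, 70%, is the share without *past-year* IPV. That share includes women whose IPV was earlier, and the design places those women in group 3. The never-exposed share implied by the 56% figure is at most 100 − 56 = 44%, if both percentages share one denominator.

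**3. Power of 193 vs 83.** Let d = p1 − p0, let p̄ be the sample-weighted rate, and let c = ½(1/193 + 1/83) = 0.0086. Then

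power = Φ{[d − c − 1.960 × √(p̄(1 − p̄)(1/193 + 1/83))] / √(p0(1 − p0)/193 + p1(1 − p1)/83)}.

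If 20% is the CP-alone rate, p0 = 0.20 and p1 = 0.40. The numerator is 0.20 − 0.0086 − 1.960 × 0.0576 = 0.0785 and the denominator is 0.0610, so power = Φ(1.287) = 90.1%. The population exposure share does not enter.

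If 20% is the study-population rate, then 0.20 = p0(1 − e) + 2p0·e, so p0 = 0.20/(1 + e), where e is the share exposed:

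| Share exposed, e | CP alone vs exposed | Power, corrected | Power, uncorrected |
|---|---|---|---|
| 30% (as stated) | 15.4% vs 30.8% | 77% | 81% |
| 46% (quota mix, 166/359) | 13.7% vs 27.4% | 71% | 76% |
| 56% (source, current or past) | 12.8% vs 25.6% | 67% | 73% |

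Moving from 30% to 56% lowers power by about 10 points, but only on this second reading of the 20%.

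**The case against.** The strongest reply is that, in the calculation that reproduces the plan, the 30% does nothing except set an allocation ratio. For fixed groups of 193 and 83 at 20% vs 40%, power is 90.1% whatever share of the population is exposed. That stands. The lower figures need the 20% to be a study-population rate, which is what the section says but not what its arithmetic uses.

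A reader might go further and infer three things that the documents do not support.

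- *That the 193 CP-alone women will include women with past IPV.* They will not. Group 1 is defined as never exposed to IPV or other violence, both are measured, and each group is filled and monitored against its own target.
- *That the recruitment channels cannot yield 193 never-exposed women.* The cited study was a mixed-sex sample from one rehabilitation center. This study recruits through IPV support centers, CP associations, CP units and primary care, and fills groups to target, so that study's mix says little about yield.
- *That the groups must be re-split.* A split such as 158 CP alone, 108 current and 93 past needs a 30:26:44 breakdown that the article does not give; it assumes one denominator for both percentages. At 20% vs 40% it would raise current vs CP alone to 92.6% but leave past vs CP alone at 90.1%.

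What the reply does not remove is the contradiction. The article defines exposure as current or past, and takes from its source a figure that it reports elsewhere as past-year only.

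**Conclusion.** The point holds as a fault in a planning input. The 30% is mislabelled relative to the article's own account of its source, and it leaves the 193:83 ratio without the justification claimed for it. It does not show the total of 359 to be too small. Under the assumed 30:26:44 breakdown, at 20% vs 40%, the same formula asks for 99 + 146 (current vs never) and 93 + 158 (past vs never), or about 99 + 93 + 158 = 350 women for three groups.

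The size of the problem depends on what the 20% means. If it is the CP-alone rate, power stays at about 90%. If it is the study-population rate, as printed, power is about 67-77%, depending on the share exposed.

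These figures assume a two-sided 5% test with continuity correction, one IPV group against CP alone, and a ratio of 2.0 for current and past IPV alike. They also treat rates from a mixed-sex, single-center sample as usable for women with CP, and past-year IPV as a stand-in for current IPV. Neither is established in the article.

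**What to change.** In the Sample Size Calculation section:

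1. Label the 30% as past-year IPV, used as an approximation to current IPV, or replace it with the 56% current-or-past figure. Note that the source is a mixed-sex sample from one center.
2. State that 20% is the assumed pain-avoidance rate in women with CP alone, as defined under Goals of This Study. If it is meant as the study-population rate, restate the power as about 67-77% instead of 90%, giving the exposure share used.
3. Report power separately for current IPV vs CP alone and for past IPV vs CP alone. With 83 in each IPV group and the same ratio, the two figures coincide; if the assumed ratio differs by group, they will not.

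Keep the total at 359. Re-splitting the targets is optional and gains little. The cost is some wording and one recalculation, with no additional women; the only downside is a lower stated power if the 20% remains a study-population figure.
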